### Exploratory outcomes

All participants will be offered the opportunity to take part in several optional study visits with a view to 20 participants completing each treatment ARM. Uptake to these optional visits will be determined by eligibility, specifically contraindications to MR scanning and patient choice.

***Euglycaemic–hyperinsulinaemic clamp:*** A subset of participants will take part in a two-stage, low-dose and high-dose euglycaemic–hyperinsulinaemic clamp combined with a [6,6 ^2^H_2_] glucose infusion, at baseline and week 32 (described in detail in Cuthbertson *et al*^25^). Briefly, a primed continuous infusion of [6,6 ^2^H_2_] glucose will be administered intravenously for 6 hours. After 2 hours, insulin infusion at 0.5 mU·kg^-1^·min^-1^ (low-dose) will be administered for 2 hours to measure the insulin sensitivity of endogenous glucose production (EGP); then insulin infusion at 1.5 mU·kg^-1^·min^-1^ (high-dose) will be administered for 2 hours to measure insulin sensitivity of peripheral glucose uptake (Rd). Euglycaemia will be maintained by adjusting a 20% glucose infusion, spiked with glucose (7 mg·g^−1^ for low dose, 10 mg·g^−1^ for high dose) according to 5 min plasma glucose measurements using a glucose oxidase method (Yellow Springs Analyser). Blood samples will be obtained before the start of the tracer infusions, every 10 min during the final 30 min of the basal period, low-dose and high-dose steady state of the clamp procedure, and every 30 min between these periods. The isotopic enrichment of plasma glucose will be determined by gas chromatography mass spectrometry at the Wolfson Centre for Translational Research, Postgraduate Medical School, University of Surrey, UK.***Doubly labelled water (DLW):*** A subset of participants will undertake the doubly labelled water method combined with a DEXA scan, at weeks 0, 4, 16 and 32 to assess mean energy expenditure over a 2-week period. Participants will drink from a stock solution of ^2^H_2_O (99% enrichment) and H_2_^18^O (10% enrichment) at a dose of 1 g·kg^-1^. Spot urine samples will be collected at 1.5-hour intervals on the day of DLW administration, followed by once daily for 13 days. Isotopic enrichments of the urine samples will be measured by isotope ratio mass spectrometry at The National Institute of Diabetes and Digestive and Kidney Disease (NIDDK), Bethesda, USA.***Endothelial function and vascular structure***: A 10 MHz multifrequency linear array probe attached to a high-resolution ultrasound machine (Siemens Medical Solutions, Malvern, Pennsylvania, USA) will be used to image the carotid artery and the brachial artery (in the distal third of the upper right arm) at baseline and week 32 in a subset of participants. Nitric oxide–mediated endothelial function will be assessed by measuring flow-mediated dilatation (FMD) in response to a 5 min ischaemic stimulus, induced by forearm cuff inflation.^26^ Peak brachial artery diameter and blood flow velocity, and the time taken to reach these peaks following cuff release will be recorded. The structure of the carotid artery will be measured as the intima-media thickness (cIMT), or artery wall thickness using custom software.^27^***Cardiac structure and function:*** Indices of myocardial systolic and diastolic function will be determined using 2D and tissue Doppler echocardiography.^28^ All echocardiograms will be performed using a GE E95 machine with an M5SC-D 2.5 MHz phased array transducer, measuring left ventricular (LV) dimensions during diastole and systole and wall thicknesses and LV mass; LV and ejection fraction (modified Simpson’s biplane method); left atrial volumes; mitral inflow peak early diastolic velocity (E), peak late diastolic velocity (A), E/A ratio and E wave deceleration time. Tissue Doppler mitral annular early diastolic velocity (E′) will be assessed at septal and lateral sites, and averaged for calculation of E/E′. Global longitudinal strain will be derived from apical 4-chamber, apical 2-chamber and apical long axis images. All data will be analysed using Echopac (V.9: GE, Horten, Norway).***Cardiac MRI:*** A subset of participants will undertake cardiac magnetic resonance at baseline and week 32 using the same MRI scanner described combined with ECG gating. A gadolinium-based contrast agent (Gadovist, Bayer) will be administered via a cannula in the forearm to facilitate imaging. A 2.5 mL blood sample will be collected to measure the haematocrit. Strain and peak early diastolic strain rate will be quantified from tagging and cine images using InTag (www.creatis.insa-lyon.fr/inTag/) and feature tracking, respectively. LV volumes, mass and function will be calculated using commercially available non-proprietary software. Tissue characterisation will be performed using standard T1 mapping (correcting for haematocrit) and late gadolinium enhancement techniques.***Functional Magnetic Resonance Imaging (fMRI):*** Using the same MRI scanner, a subset of participants will undergo fMRI to examine neural processing in response to tasks that assess reward related function (Passive-Viewing) and inhibitory control (Stop-Signal Task).^29^ Using the test-meal protocol described earlier, BOLD imaging will be conducted in patients under fasted (pre-lunch) and sated (post-lunch) states both at baseline and week 32. The fMRI data will be imported to and analysed using Statistical Parametric Mapping software (SPM12, University College London, UK) and custom built MATlab scripts (The MathWorks, Massachusetts, USA). Appetite will be measured throughout the scanning day using a VAS.

### Monitoring/dispensing visits (1, 4, 5, 6, 7, 8, 9, 10)

These visits will involve a brief consultation with the study team to review glycaemic control (self-monitored capillary blood glucose), adverse effects and compliance (tablet count), and to collect supply of medication. All injections of exenatide QW/placebo will be administered weekly by unblinded staff members at site and recorded. Unblinded members of the research team will have no role in assessment of participants outside of these specified roles as detailed in the trial delegation log.

### Pharmacovigilance

All adverse events will be reported and assignment of the severity/grading (mild, moderate, severe, life-threatening, death) made by the investigator responsible for the care of the participant. The assignment of causality will be made by the investigator. All non-serious adverse events (SAEs), whether expected or not, will be recorded and updated at each study visit. All new SAEs will be reported from the point of consent until 28 days after discontinuation of the investigational medical product; this includes those thought to be associated with protocol-specified procedures. Investigators will report SAEs, serious adverse reactions (SARs) and sudden unexpected adverse reactions (SUSARs) to LCTC within 24 hours of the local site becoming aware of the event. LCTC will notify the Medicines and Healthcare products Regulatory Agency (MHRA) and main Research Ethics Committee (REC) of all SUSARs occurring during the study: fatal and life-threatening SUSARs within 7 days of notification and non-life-threatening SUSARs within 15 days. All adverse events will be followed until satisfactory resolution or until the investigator responsible for the care of the participant deems the event to be chronic or the patient to be stable.

### Trial monitoring and oversight committees at LCTC

The RESILIENT study will have a Trial Management Group (TMG), Trial Steering Committee (TSC) and an Independent Safety and Data Monitoring Committee (ISDMC) to monitor study progress.

The TMG, supported by the LCTC, will be responsible for the day-to-day running and management of the trial and will consist of the protocol committee members and the trial manager. The TSC will provide oversight of the study, concentrating on progress of the study, adherence to protocol, participant’s safety and consideration of new information, making recommendations on study pathway modifications and continuation of the study. The TSC will include experienced lay members of the public, other medical experts and clinical trialists. Meetings will be held at regular intervals determined by need, but no less than once a year. The ultimate decision for the continuation of the trial lies with the TSC.

The ISDMC will be responsible for reviewing and assessing recruitment, interim monitoring of safety and effectiveness, trial conduct and external data. The ISDMC will also provide recommendations to the TSC concerning continuation of the study.

### Outline of analysis

#### General approach

Categorical variables will be summarised as frequency (%), and continuous variables will be summarised as mean (SD) or median (IQR) depending on the distribution. Full details of the planned statistical analysis will be included in a separate statistical analysis plan to be developed in the months following trial opening and will be approved by both the ISDMC and the TSC.

##### Subgroup analysis

No subgroup analysis is planned for this trial.

##### Significance levels

For the analysis of the primary outcome, statistical significance will be tested using Hochberg’s procedure, a hierarchical analysis approach for the primary outcomes of (1) exenatide QW and dapagliflozin compared with placebo control, (2) dapagliflozin alone compared with placebo control. Here comparisons will be ordered (descending) in terms of their significance level and assessed using a p value <0.05 to determine statistical significance for the first comparison and p<0.025 for the second.

The main analysis for primary and secondary endpoints will use the full analysis set, consisting of all randomised patients, with participants analysed according to the group to which they were originally allocated, and with outcomes included irrespective of protocol adherence, in order to follow the *intention-to-treat* principle. The safety population, consisting of all patients who actually receive a trial intervention, according to the treatment received, will be used for analysis of toxicity and adverse events.

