## Primary objective

The primary objective of the study is to compare the adjusted mean reduction in total body fat mass (determined by dual-energy X-ray absorptiometry, DEXA) from baseline following 32 weeks of treatment with exenatide QW and dapagliflozin versus dapagliflozin alone compared with control (placebo).

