### Sample size

This trial will examine exenatide QW, a weekly GLP1-RA, added to dapagliflozin versus sham saline injection added to dapagliflozin for an intervention period, of 32 weeks compared with a control group (placebo tablet and sham injection).

**Arm A:** Placebo tablet once daily and sham injection once weekly.**Arm B:** SGLT2 (dapagliflozin 10 mg once daily plus sham injection once weekly).**Arm C:** SGLT2+GLP1 RA (dapagliflozin 10 mg plus exenatide 2 mg once weekly injection).

The sample sizes have been calculated in order to conduct the following two comparisons:

Arm B (dapagliflozin) vs A (placebo).Arm B (dapagliflozin) vs C (dapagliflozin and exenatide).

These comparisons are selected to answer the key question of interest; although the study will not provide comparisons between arms C and A, nor will they be reported.

The original sample size calculation was carried out using Stata V.14 software (Stata Statistical Software: Release 14. College Station, Texas, USA: StataCorp LP). For both comparisons, a 1.5 kg in the change in body fat mass is considered a clinically relevant difference. From previous data, the within patient SD for the change in total body fat between baseline and 32 weeks is estimated as 1.8 kg.^17^ From this, a between-patient SD of 2.55 kg was computed. Using a two-group test with equal means (assuming 80% power and one-sided 5% significance level), 36 patients per treatment arm were estimated to be required in order to adequately power the planned analysis (assuming effect size of 0.59). Using these calculations and an anticipated 10% attrition and patient dropout rate, the original sample size was set at 120 participants.

As a result of the COVID-19 pandemic, however, 15 active patients were lost to follow-up and a revised sample size calculation was implemented, reducing the original sample size from 120 patients to 110 randomised patients in order to maintain meaningful results within the remaining timeframe of the study. Using the same clinically relevant difference of 1.5 kg, significance level and power, the between-patient SD would be 2.42 kg, giving an effect size of 0.62. Assuming 80% power, a minimum of 33 patients per treatment arm are required. Allowing for an anticipated 11% attrition rate/dropout rate, a total of 110 patients are required (calculated using NQuery V.8.1.2.0).

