#### Analysis

For analysis of the primary endpoint, the mean difference from baseline and week 32 will be presented with a corresponding 95% CI. Between-group differences will be analysed using linear regression techniques, analysing the week 32 values while including baseline covariate value. The effect of dapagliflozin will be estimated by contrasting (1) control arm versus dapagliflozin arm. The effect of exenatide will be estimated by comparing (2) dapagliflozin versus dapaglifozin and exenatide.

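### The Hochberg family tests combination vs placebo, a comparison the protocol bars, and omits combination vs dapagliflozin, the add-on question the trial was sized to answer

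*Protocol article*

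**What the plan says.** Arm A is placebo tablet plus sham injection, arm B is dapagliflozin plus sham injection, and arm C is dapagliflozin plus exenatide.

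- **Sample size.** Two comparisons are sized: "Arm B (dapagliflozin) vs A (placebo") and "Arm B (dapagliflozin) vs C (dapagliflozin and exenatide"). The section presents these as the comparisons that answer the key question, and adds "although the study will not provide comparisons between arms C and A, nor will they be reported".
- **Analysis.** The primary model contrasts control with dapagliflozin for the dapagliflozin effect. For the other: "The effect of exenatide will be estimated by comparing (2) dapagliflozin versus dapaglifozin and exenatide".
- **Significance levels.** Hochberg's procedure for the primary outcome is applied to "1) exenatide QW and dapagliflozin compared with placebo control, (2) dapagliflozin alone compared with placebo control", with the ordered comparisons "assessed using a p value <0.05 to determine statistical significance for the first comparison and p<0.025 for the second".
- **Primary objective** (repeated in the Abstract). Fat mass reduction is compared for "treatment with exenatide QW and dapagliflozin versus dapagliflozin alone compared with control (placebo"). All three arms are named, but the pairs to be tested are not.

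**The concern.** The Significance levels section is the only place that sets a decision rule for the primary outcome, and its pair of contrasts differs from the pair that the trial is sized for and models. It assigns alpha to C vs A, which the Sample size section says will be neither provided nor reported. It assigns none to B vs C.

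B vs C is the scientific point of the trial. The strengths and limitations box says the study investigates what adding a GLP-1 receptor agonist to an SGLT2 inhibitor may induce, and the central hypothesis in the Background concerns adding exenatide to dapagliflozin. C vs A cannot stand in for it, because the combination can beat placebo through dapagliflozin alone. If the text stands, the confirmatory claim concerns the wrong contrast, the add-on result has no error control, and the choice between two published families could be made after the results are known.

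**Working it through.** **The contrasts side by side**

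| Contrast | Sample size | Analysis | Significance levels |
|---|---|---|---|
| B vs A | sized | estimated | in the Hochberg family |
| C vs B | sized | estimated | absent |
| C vs A | barred | not mentioned | in the Hochberg family |

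**Inputs** (all from Sample size): difference 1.5 kg for each sized comparison; revised between-patient SD 2.42 kg; 33 per arm; 80% power; one-sided 5%. The Significance levels section does not state sidedness, so both readings are shown.

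**The plan's own figure.** n per arm = 2(z₀.₉₅ + z₀.₈₀)² / (δ/SD)², with δ/SD = 1.5/2.42 = 0.620. This gives 2 × (1.645 + 0.842)² / 0.620² ≈ 32.2, so 33. The stated 33 is reproduced. A two-sided 5% test would give 41.

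**Power of a single comparison at 33 per arm.** SE = 2.42 × √(2/33) = 0.596 kg, so 1.5/0.596 = 2.52.
- One-sided 0.05: Φ(2.52 − 1.645) = 81%.
- Two-sided 0.05: Φ(2.52 − 1.960) = 71%.

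**Simulation.** Arm means were drawn as normal with known SD 2.42 kg and n = 33 per arm, 500,000 replicates. Hochberg rule: if the larger p-value is below 0.05, reject both; otherwise reject the comparison with the smaller p-value if it is below 0.025.

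| Quantity | One-sided | Two-sided |
|---|---|---|
| *Family as written, {C–A, B–A}* | | |
| C vs A declared significant when B and C both beat A by 1.5 kg (exenatide adds 0) | 78% | 68% |
| Power for C vs A when each step is worth 1.5 kg (C–A = 3.0 kg) | >99% | >99% |
| Any false positive among these two tests, global null | 4.8% | 4.8% |
| Any false positive if C vs B is also tested at an unadjusted 0.05, global null | 8.9% | 8.6% |
| *Family as sized and modelled, {B–A, C–B}* | | |
| Any false positive, global null | 5.0% | 4.8% |
| Power for C vs B, both effects 1.5 kg | 80% | 69% |
| Power for C vs B, only C vs B real | 72% | 61% |

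Using t-tests with pooled variance instead of known SD changes these figures by about one percentage point or less.

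**The case against.** Two of the three operative sections agree with each other, so the mismatch is probably a labelling slip in Significance levels and not a plan to abandon the add-on question. B vs C is still sized and estimated. An analysis plan not shown here may already have the right pair. All of this is plausible, but none of it removes the contradiction. The article states two incompatible families, so this is not a detail left to the analysis plan.

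Four cautions on the figures stand:
- The error of about 9% belongs to a hybrid in which C vs A is tested despite being barred and C vs B is tested at 0.05. No section assigns C vs B that level, so this is one possible consequence of the conflict and not the plan's stated error rate.
- The 78% or 68% is not a false-positive rate. In that scenario C truly beats A; the result simply says nothing about exenatide.
- The gap between 81% and 71% power for C vs B comes from sidedness, not from the family conflict.
- The >99% power for C vs A assumes that two 1.5 kg steps add up. The plan gives 1.5 kg for the two sized comparisons only.

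**Conclusion.** The concern holds. The protocol's decision rule for the primary outcome includes a comparison that the protocol forbids and leaves out the comparison that tests its hypothesis. The lack of control is one of multiplicity: B vs C will be estimated, but no significance level or place in the testing procedure is assigned to it.

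The contradiction rests on the text alone and needs no assumption. Its numerical consequences assume normal data, 33 evaluable patients per arm, SD 2.42 kg and steps of 1.5 kg. The conclusion is the same for one-sided and two-sided tests. Because the section determines which primary claim the trial can make, it must be corrected before unblinding.

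**What to change.** In Significance levels, define the Hochberg family as exactly (1) B vs A and (2) C vs B, and remove C vs A. Reword the primary objective, there and in the Abstract, as these two pairwise contrasts. Check that the analysis plan names the same pair, and state the sidedness of the 0.05 and 0.025 thresholds.

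The two contrasts share arm B with opposite sign (correlation −0.5), so the positive-dependence condition usually cited for Hochberg is not met for one-sided tests. The simulated error of 5.0% shows no practical loss of control here, but the plan should say so.

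The cost is a wording amendment before unblinding, with no added patients or procedures. The sample size carries no allowance for multiplicity. On the one-sided basis used for sizing, power for C vs B is about 80% if both effects are 1.5 kg and about 72% if only the exenatide effect is real. Guaranteeing 80% when C vs B must pass at one-sided 0.025 would take 41 per arm (42 by t-test). That is a separate decision and is not needed to correct the family.

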##### Missing data

Missing data are assumed to be small and analysis will be carried out on a complete case basis. If there are a significant number of missing entries on any endpoint (>20% for example), missing data shall be estimated using multiple imputation based on the method of chained equations.

#### Analysis

For analysis of the primary endpoint, the mean difference from baseline and week 32 will be presented with a corresponding 95% CI. Between-group differences will be analysed using linear regression techniques, analysing the week 32 values while including baseline covariate value. The effect of dapagliflozin will be estimated by contrasting (1) control arm versus dapagliflozin arm. The effect of exenatide will be estimated by comparing (2) dapagliflozin versus dapaglifozin and exenatide.

##### Secondary analyses

Analyses of all secondary endpoints are continuous and analysis techniques shall replicate that of primary endpoints.

#### Safety analysis

Information relating to adverse events (including events relating to hypoglycaemia, gastrointestinal upset, and urinary and genital tract infections) will be tabulated and summarised descriptively. Continuous laboratory values will be summarised as described above.

## Ethics and dissemination

This study is being conducted in accordance with Good Clinical Practice (GCP), as defined by the International Conference on Harmonisation (ICH) and in compliance with the European Union Directive 2001/20/EC transposed into UK law as statutory instrument 2004 No 1031: Medicines for Human Use (Clinical Trials) Regulations 2004 and all subsequent amendments and the US Code of Federal Regulations, Title 21, Part 50 (21CFR50). The trial protocol has received the favourable opinion of the NRES North West/Liverpool Central Research Ethics Committee (14/NW/1147; protocol number UoL 001187). An appropriate patient information sheet and consent forms describing in detail the trial interventions/products, trial procedures and risks were approved by the ethical committee (IEC), and the patients are asked to read and review the document. The investigator explains the study to the patient and answer any questions posed. A contact point where further information about the trial may be obtained is provided. After being given adequate time to consider the information, the patient is asked to sign the informed consent document. A copy of the informed consent document is given to the patient for their records and a copy placed in the medical records, with the original retained in the investigator site file. The patient may withdraw from the trial at any time by revoking the informed consent. The rights and welfare of the patients are protected by emphasising to them that the quality of medical care will not be adversely affected if they decline to participate in this study.

## Regulatory approval

This trial has been registered with the MHRA and has been granted a Clinical Trial Authorisation (CTA). The CTA reference is its EudraCT number: 2013-004264-60.

## Publication

The results will be analysed together and published as soon as possible. The uniform requirements for manuscripts submitted to *biomedical journals* (http:// www.icmje.org/) will be respected. The ISRCTN allocated to this trial would be attached to any publications resulting from this trial.

